### Participant timeline

Figure 3 shows the timeline and criteria for assessments.

**Fig. 3 Fig3:**
[figure not shown]
Timeline and criteria for assessments

### Determination of sample size

Non-inferiority will be demonstrated if the rate of patients in complete remission at 1 year after randomization does not differ by more than ΔL=−5%. Setting the significance level at 0.025 (one-sided) and a power of 80% requires a sample size of 598 patients without Tg antibodies (299 per group) (Nquery software).

In this network’s previous study, 94% of the low-risk patients (including 12% T2N0) were in complete biological remission at 1 year after randomization [40]. In a similar prospective multicenter trial, 90.2% of the low-risk patients, including patients T1-T3 N0-N1 with or without central compartment neck dissection, were in complete biological remission at 1 year [42].

If 5% secondary exclusion (final histopathology not differentiated thyroid cancer): 628 patients are required for randomization.

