**Trial design and methods:**

Prospective randomized open multicenter phase III trial including patients with 11–40-mm papillary thyroid carcinoma (Bethesda VI) or suspicious cytology (Bethesda V) confirmed malignant on intra-operative frozen section analysis, with no suspicious lymph nodes on a specialized preoperative ultrasound examination. Patients will be randomized 1:1 into two groups: the reference group total thyroidectomy with bilateral prophylactic central neck dissection, and the comparator group total thyroidectomy alone. All patients will receive an ablative dose of 30mCi of radioactive iodine (RAI) within 4 months of surgery. The primary outcome is to compare the rate of excellent response at 1 year after surgery between the groups, as defined by an unstimulated serum thyroglobulin (Tg) level ≤ 0.2 ng/mL with no anti-Tg antibodies, an normal neck ultrasound and no ectopic uptake on the post-RAI scintiscan. Non-inferiority will be demonstrated if the rate of patients with excellent response at 1 year after randomization does not differ by more than 5%. Setting the significance level at 0.025 (one-sided) and a power of 80% requires a sample size of 598 patients (299 per group). Secondary outcomes are to compare Tg levels at 8 +/− 2 postoperative weeks, before RAI ablation, the rate of excellent response at 3 and 5 years, the rate of other responses at 1, 3, and 5 years (biochemical incomplete, indeterminate, and structurally incomplete responses), complications, quality of life, and cost-utility.

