Our study differs from these published studies in the following ways:Our study includes only tumors ≥11 mm (microcarcinomas are not eligible), whereas all of the studies cited in Table 1, with the exception of the study by Sippel et al. [32], included a large proportion of microcarcinomas (in Ahn et al. [31] for example, 90% of the tumors were T1 with a mean tumor size of 1.1 +/− 0.6 cm);Thyroglobulin measurements will be evaluated before and after the administration of RAI to evaluate the effect of RAI ablation and eliminate this bias found in most of these studies in which outcomes were evaluated after RAI ablation in most or all patients;Finally, our study is designed with a non-inferiority margin of 5% and an alpha level set at 0.025, whereas the study by Viola et al. [34] is significant but with a non-inferiority margin of 15% and an alpha of 0.05.

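### The 80% power of 598 patients rests on an unstated remission rate of about 95% in both arms, above both rates the protocol cites (94% and 90.2%)

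*Protocol article*

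**What the plan says.** The sample size section of the protocol article sets non-inferiority as established if "the rate of patients in complete remission at 1 year after randomization does not differ by more than" the margin of −5%. It continues: "Setting the significance level at 0.025 (one-sided) and a power of 80" percent lead to the size, namely that "a power of 80% requires a sample size of 598 patients without Tg antibodies (299 per group"). The abstract (Trial design and methods) repeats it: "a power of 80% requires a sample size of 598 patients (299 per group"). Allocation is equal: "Patients will be randomized 1:1 into two groups". The background section confirms the error rate: "our study is designed with a non-inferiority margin of 5% and an alpha level set at 0.025".

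No assumed remission rate is given for either arm. Two rates follow the size statement. For the network's previous study the text reports that "94% of the low-risk patients (including 12% T2N0) were in complete biological remission at 1 year after randomization". For a similar multicentre trial it reports "90.2% of the low-risk patients, including patients T1-T3 N0-N1", with or without central neck dissection. The Primary objective section gives the same two figures. A remission rate of 95% is printed nowhere in the article's text.

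**The concern.** A reader will take the two cited rates as the basis for 598, because they are the only rates offered, and neither leads to that number. Near the top of the scale the variance p(1−p) rises quickly as the rate falls, so one or two points of optimism in the planning rate cost a good deal of power.

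What is at stake is the chance of an inconclusive trial. If thyroidectomy alone is truly equivalent, the plan accepts a 20% risk of failing to show non-inferiority. At the cited rates that risk would be larger. No interim analysis is planned. An inconclusive result could then be read as support for neck dissection by someone who believes that the trial had 80% power.

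**Working it through.** **Inputs from the article.** Margin 0.05 (absolute), one-sided alpha 0.025, power 80%, 1:1 allocation, 299 evaluable patients per group, cited rates 0.94 and 0.902. **Assumption made here:** both arms have the same true rate p. The article states no difference.

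**Formulas** (unpooled normal approximation):

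- n per group = (z0.975 + z0.80)² × 2p(1−p) / 0.05², with (1.960 + 0.842)² = 7.849
- power = Φ(0.05 / √(2p(1−p)/299) − 1.960)

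**Reproducing the plan's figure.** At p = 0.95: 7.849 × 0.0950 / 0.0025 = 298.3, so 299 per group and 598 in total. Solving the formula for n = 299 gives p = 94.99%.

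**The same formula at the cited rates:**

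- p = 0.94: 7.849 × 0.1128 / 0.0025 = 354.1, so 355 per group (710 in total)
- p = 0.902: 7.849 × 0.1768 / 0.0025 = 555.05, so 556 per group (1,112 in total)

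**Power with 299 per group:**

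| True rate, both arms | Standard error | 0.05/SE − 1.960 | Power | Exact binomial power of the Wald interval rule |
|---|---|---|---|---|
| 95% | 0.01782 | 0.845 | 80.1% | 80.5% |
| 94% | 0.01942 | 0.614 | 73.0% | 73.4% |
| 90.2% | 0.02432 | 0.096 | 53.8% | 54.2% |

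At rates above 95% the power is higher: 84% at 95.5% and 88% at 96%.

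**Other formulas at one-sided 0.025.** They do not bring 299 closer to the cited rates. With a continuity correction the sizes per group are 338 (95%), 394 (94%) and 595 (90.2%). With the Farrington–Manning variance they are 334, 384 and 572.

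**Unequal true rates.** With 299 per group, 80% power is also reached if thyroidectomy alone is truly a little better: about 94.4% against 94%, or 91.8% against 90.2%.

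**Alpha taken from the analysis section.** The statistical methods section bases the decision on a one-sided 95% confidence interval. Read literally, that is one-sided alpha 0.05. With 299 per group, power would then be 82% at 94% and 66% at 90.2%.

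**The case against.** The strongest reply is that nothing has been miscalculated. The number 598 is exactly right for 95% in both arms, and the article never says that it was derived from 94% or 90.2%. The article also condenses a longer protocol that may state the planning rate. This much stands: the finding is an unstated and favourable assumption, not an arithmetic error. It does not remove the point, because the article prints a power claim next to two supporting rates that do not support it.

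A second reply is that power depends on the true rate, which nobody knows. That also stands. A reader might infer that the trial simply does not have 80% power. The documents do not show that, since a true rate of about 95% or more would deliver it.

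A reader might also argue that the rate here must be lower than those cited: the sample size section calls them biological remission, while the primary endpoint adds a normal SPECT-CT and a normal ultrasound. The documents do not support that step. The Primary objective section presents the same figures as complete remission, right after defining the three-part endpoint. The populations also differ in both directions. The 94% cohort had only 12% T2N0, whereas this trial takes tumours of 11–40 mm. The 90.2% cohort included T3 and N1 patients, whom this trial excludes at clinical staging. This trial's primary analysis set also leaves out patients with detectable anti-Tg antibodies, and how the cited studies handled them is not visible.

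Finally, the literal one-sided 95% interval would lift the power at 94% above 80%. It conflicts with the 0.025 stated in the abstract, the background and the sample size section, and it still falls short at 90.2%. It does not rescue the stated design, but it does mean that the power figures depend on how that conflict is settled.

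**Conclusion.** The point holds as a matter of an undisclosed planning assumption. At the stated margin and one-sided 0.025, 598 evaluable patients give 80% power only if remission is about 95% or higher in equal arms. The protocol does not state that rate, and both rates it cites are lower. At 94% the power is about 73%, so the risk of missing true non-inferiority is 27% instead of 20%. At 90.2% the power is about 54% and the risk 46%.

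These figures assume equal true rates, 299 evaluable patients per group actually reached, and one-sided 0.025. The 90.2% case is the more pessimistic one and comes from a cohort broader in stage. The type I error is not affected: lower power makes an inconclusive result more likely, not a false claim of non-inferiority.

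**What to change.** In the sample size section and in the abstract:

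- State the remission rate assumed in each arm and why it is expected, including why it exceeds the two cited rates if 95% is what was used.
- Restate the power of 598 evaluable patients as about 80% at 95%, 73% at 94% and 54% at 90.2%, for equal arms.
- Note that the 90.2% cohort covered T1–T3 and N0–N1.
- Say that these figures use one-sided 0.025, and reconcile the one-sided 95% interval in the statistical methods section with that level.

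This is a change of wording. It needs no extra patients and leaves the margin, the design alpha and the endpoint as they are. The only cost is a less favourable stated power.

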### Criteria for discontinuing or modifying allocated interventions

Secondary exclusion will be performed for patients in whom final pathology (non-frozen section analysis but defintive pathological evaluation) does not confirm the presence of a differentiated thyroid cancer.

In no other instances does this study provide for discontinuing or modifying allocated interventions.

Reasons for withdrawal from the trial (study interventions and follow-up) may include:Lost to follow-upWithdrawal of consentDeath

If a patient does not return for a scheduled visit, every effort will be made to contact them. In any case, every effort will be made to document the patient outcome and all attemps should be documented in the corresponding medical file. The investigator will inquire about the reason for withdrawal, request the patient to return for a final visit, if applicable, and follow up with the patient regarding any unresolved adverse events. The early termination final visit should include all assessments listed for the End of Study visit.

If the patient withdraws their consent for the study, no further study-specific evaluations will be performed, and no additional data will be collected. The sponsor may retain and continue to use any data and samples collected before such refusal except in case of patient opposition. Any opposition will be transmitted by the investigator to the sponsor without undue delay.

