### Statistical methods

#### Statistical methods for primary and secondary outcomes

Descriptive summary statistics will be provided for continuous demographic, laboratory, and clinical variables. The descriptive summary statistics will include number of patients, means and standard deviations for quantitative variables, and percentages for qualitative data.

Subject demographic and baseline characteristics will be summarized by treatment group. The Student test will be used for the continuous variables (or non-parametric test if variables are not normally distributed), and the chi-square test will be used for the categorical variables.

Primary outcomes s1

The main endpoint will be analyzed 1 year after randomization of the last patient, once all the CRF will have been collected and the database has been cleaned. The analysis will be performed when all patients will have 1 year of follow-up, and no lost of follow-up will be tolerated.

A patient will be in remission if the requirements are met at 1 year following randomization. Conversely, a patient will be considered to not be in remission if the criteria are not met at 1 year following randomization. In the absence of censored data, the proportion of patients in complete remission will be calculated as a percentage.

Since the study is designed as a non-inferiority study, the primary analysis will be carried out by considering all evaluable patients (per-protocol population), as this is the most conservative approach in this context. Patient will be considered as evaluable if the treatment and the follow-up conform to the study protocol (diagnostic tests performed) and if the patient does not have detectable anti-Tg antibodies. A sensitivity analysis using the intent-to-treat (ITT) population, considering all patients in their initial group of randomization, will also be performed, to test the robustness of the results.

The observed difference in patients in complete remission (∆) and its 95% unilateral confidence interval will be calculated. If the unilateral confidence interval does not include the −5% clinically relevant difference (∆L), then the TT alone strategy will be considered as non-inferior to the TT + PCND strategy.

All statistical analyses will be performed using the SAS® software.

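### The randomisation total of 628 allows only for histology exclusions, although the primary analysis also drops antibody-positive and non-conforming patients, so 80% power is not supported for that population

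*Protocol article*

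**What the plan says.** The Protocol article, Determination of sample size, sets the requirement at "598 patients without Tg antibodies (299 per group"), for 80% power at one-sided 0.025 with a 5-point margin. It then makes one adjustment for loss: "If 5% secondary exclusion (final histopathology not differentiated thyroid cancer): 628 patients are required for randomization".

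Statistical methods for primary and secondary outcomes makes the per-protocol set primary. A patient is evaluable only if treatment and follow-up followed the protocol, with the diagnostic tests done, and "if the patient does not have detectable anti-Tg antibodies". The section on protocol non-adherence and missing data repeats this rule. The intention-to-treat analysis is a sensitivity analysis.

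TgAb status appears in neither the inclusion nor the non-inclusion criteria, and it is not in the baseline assessment list. The Follow-up section first schedules it at 8 ± 2 weeks after the operation. Randomisation takes place before surgery or in the operating room.

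On attrition, the statistical section says that loss to follow-up will not be accepted. The section on discontinuing or modifying interventions nevertheless foresees it: "Reasons for withdrawal from the trial (study interventions and follow-up) may include" loss to follow-up, withdrawal of consent and death.

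**The concern.** The number 598 is defined after antibody-positive patients have been removed. It is the size of the primary analysis set, not of the randomised cohort. The step from 598 to 628 should therefore cover every route by which a randomised patient leaves that set. It covers one route, final histology that is not differentiated thyroid cancer. Two others written into the evaluability rule, detectable TgAb and non-conforming treatment or tests, have no allowance.

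What is at stake is power, not type I error. In a non-inferiority trial, a smaller primary set widens the confidence interval around the difference. That raises the chance of an inconclusive answer to the main question when the two strategies are in fact equally effective.

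**Working it through.** **Inputs from the protocol.** "Setting the significance level at 0.025 (one-sided) and a power of 80"%; margin, "does not differ by more than ΔL=−5"%; "Patients will be randomized 1:1 into two groups"; 598 evaluable TgAb-negative patients; 5% histology exclusion; 628 randomised.

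**Inputs not in the protocol.** (a) The remission rate used for the calculation is not stated, so it is back-calculated below. (b) No TgAb or non-conformity rate is given, so a range t = 5% to 20% is assumed. Losses are taken as equal in the two arms.

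**Step 1: reproduce 598.** Unpooled normal approximation with equal true rates p:

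n per arm = (1.96 + 0.8416)² × 2p(1 − p) / 0.05²

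With p = 0.95: 7.849 × 0.095 / 0.0025 = 298.3, rounded up to 299 per arm, or 598. The plan's figure is reproduced, so 95% is used throughout.

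**Step 2: reproduce 628.** 598 × 1.05 = 627.9, so 628. Dividing by the retained fraction gives 598 / 0.95 = 629.5, so 630. The gap is two patients.

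**Step 3: what 628 leaves after the budgeted loss.** 628 × 0.95 = 596.6, just under 598. From the other side, 1 − 598/628 = 4.8% is the largest loss from all causes together that still leaves 598. The 5% for histology already uses that up.

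**Step 4: add the exclusions that have no allowance.** With N evaluable patients in total:

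N = 628 × 0.95 × (1 − t)

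Power = Φ(0.05 / √(2 × 0.95 × 0.05 / (N/2)) − 1.96)

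Worked example, t = 10%: N = 536.9, or 268.5 per arm; standard error = √(0.095 / 268.5) = 0.01881; 0.05 / 0.01881 − 1.96 = 0.698; Φ(0.698) = 75.7%.

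| Further loss t (assumed) | Evaluable of 628 | Power at 95% remission | Randomised needed for 598: 598 / (0.95(1 − t)) |
|---|---|---|---|
| none | 596.6 | 80.0% | 630 |
| 5% | 567 | 78.0% | 663 |
| 10% | 537 | 75.7% | 700 |
| 15% | 507 | 73.3% | 741 |
| 20% | 477 | 70.8% | 787 |

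For reference, power with all 598 evaluable is 80.1%. The same table applies whether t is made up of TgAb-positive patients, non-conforming patients or both.

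**The case against.** **The size is unknown.** A reader might infer that 628 cannot yield 598, or that the primary set will be clearly smaller. The documents do not go that far. The 5% histology loss is itself conditional, entry requires malignant cytology or frozen-section confirmation, and no TgAb rate is given. If all losses together stayed at or below 4.8%, 598 would be reached. What stands is that the plan's own 5% already uses up the allowance.

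**The formula slip is trivial.** This is right. Using 628 instead of 630 costs about 0.1 point of power (80.0% against 80.1%) and would not merit a point by itself.

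**Loss to follow-up is excluded by design.** The statement that none will be accepted explains why there is no follow-up allowance, and it sits awkwardly with the withdrawal reasons listed elsewhere. Even taken at face value, it does not cover a patient who completes follow-up with detectable TgAb, or one whose treatment did not conform.

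**The intention-to-treat analysis keeps these patients.** It does, but only as a sensitivity analysis. The primary endpoint requires absence of TgAb, so applied literally it would count antibody-positive patients as not in remission.

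**The article is condensed.** The full protocol may say more, and the timeline figure is not shown. But the article does not leave the calculation out: it states the target, the single loss and its cause, and the total, and these do not match its own evaluability rule.

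**Conclusion.** The point holds. The sample-size section defines its target as TgAb-negative evaluable patients but inflates only for histology, while the primary analysis also removes antibody-positive and non-conforming patients who are eligible for randomisation. The stated 80% power is therefore not supported for the per-protocol population. Relative to 80.1% at 598, an assumed further loss of 5% to 20% costs about 2 to 9 points of power.

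These figures rest on 95% remission in both arms (inferred, not stated), equal losses between arms, the plan's 5% histology loss and an assumed range for t.

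A reader might also combine this with the 94% and 90.2% remission rates cited in the same section and arrive at much lower power. That belongs to a different question, namely which remission rate the design uses, and the resulting fall should not be attributed to the missing allowance. Nor does the point imply bias or an inflated type I error.

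**What to change.** In Determination of sample size, state the expected fractions of TgAb-positive and of non-conforming patients. Rates pooled across arms from patients already accrued (accrual began in August 2018) can supply them without unblinding the comparison. Then restate the expected evaluable number and the power that the planned 628 gives in the per-protocol population, and name the remission rate used. In the same edit, replace multiplication by 1.05 with division by 0.95, so that the histology-only figure reads 630.

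The cost is a recalculation and a few sentences. No extra enrolment is needed if the power is simply restated; the downside is a somewhat lower stated power. If the sponsor prefers to hold 80%, the last column of the table shows what randomisation total each assumed loss would imply.

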### Recruitment

Recruiting centers belong to the ENDOCAN-TuThyRef network and are regionally in France high-volume referral centers regularly performing clinical trials on thyroid cancer. This network has already participated in and completed two prospective randomized trials on low-risk differentiated thyroid cancer: the ESTIMABL trial [40] and the ESTIMABL2 trial [41].

## Assignment of interventions: allocation

### Sequence generation

Patients will be prospectively included in the study in 2 steps:Patients will first be registered, after check of eligibility criteria and signature of the informed consent form, before any trial related procedure.Randomization (and validation of the inclusion) will then be performed: (1) before surgery for patients with malignant cytology (Bethesda 6) or (2) in the operating room, after total thyroidectomy and after confirmation of malignancy by intra-operative frozen section analysis for patients with suspicious cytology (Bethesda 5). Randomization will be performed online or by fax with the Trial Master program.

Randomization will be performed online or by fax with the Trial Master program. Patients will be randomly allocated to one of the two treatment groups, based on blocks of participants, stratified by tumor size (cT1b vs cT2) and site (to ensure a balance between the treatment groups at each site). The blocking and stratification measures will not be revealed to those enrolling patients or those allocating the interventions.

Once randomized, patients must be treated as defined in the assigned group and cannot change.

Inclusion/registration and randomization will be performed online or by fax, using the TrialMaster program, and electronically centralized by the Biostatistics and Epidemiology Unit at Gustave Roussy. A fax or an internet access in the operating room or at proximity is then mandatory. In case of any kind of problem, the investigator will contact the study data manager.

The data manager email address, phone, and fax number will be notified in the CRF. In case of any emergency or in the absence of the study data manager, an on-duty data manager will available.

